Randomized controlled study

(2) Study outline

| **Assessment**  • Primary endpoint: HbA1c  • Secondary endpoints: periodontal status, blood sugar, oxidative stress, and QOL  **Oral hygiene instruction group**  Receives oral hygiene instruction  Recruitment of study participants  **Non-surgical periodontal treatment group**  Receives oral hygiene instruction + scaling and root planning, professional toothbrushing and mechanical tooth cleaning |
| --- |

Figure. Study flow chart

Type 2 diabetes patients in the Nephrology, Diabetology and Endocrinology Department of Okayama University Hospital who consent to participate in the study will be introduced to the Department of Preventative Dentistry outpatient clinic. One member of the research group will separate patients into two groups, the oral hygiene instruction group and the non-surgical periodontal treatment group, using a table of random numbers (the patients will be asked not to inform the examiners of the group to which they are assigned). Thereafter, two dentists blinded to the group assignments will conduct periodontal examinations. Other dentists will then be in charge of oral hygiene instruction and periodontal treatment. For the periodontal examination, calibration will be repeated in advance until the kappa value (a reliability assessment index) exceeds 0.8 for inter- and intra-operator agreement.

The periodontal examination includes probing pocket depth, clinical attachment level (distance from the border between the tooth crown and root to the bottom of the periodontal pocket), bleeding on probing (whether bleeding is seen when the periodontal pocket depth is measured), and the degree of plaque buildup.

Blood tests are routinely conducted as part of regular medical examination in the Nephrology, Diabetology and Endocrinology Department (and will be arranged so that examinations are conducted in the Nephrology, Diabetology and Endocrinology Department and the Department of Preventive Dentistry on the same day). In blood tests, glycated hemoglobin (HbA1c) and glycated albumin will be assessed. Remnant blood from examinations (blood that would otherwise be disposed of as medical waste) will be used by the research group for measurement of the oxidative stress balance.

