
(3) Safety assessment

Not applicable.

8. Observation and test items

(1) Patient characteristics: Chart number, patient’s initials, sex, date of birth, race, inpatient or outpatient, height, weight, complications, past medical history, history of present illness, previous treatment, and other.

(2) Confirmation of subjective and objective symptoms: Confirmation by interview (with reference to the symptom diary if available).

(3) Blood test: Same test items as in regular medical examination.

(4) Blood biochemistry test: Same test items as in regular medical examination. Factors associated with oxidative stress will also be assessed to confirm the relationship between oral health and whole body status.

(5) Periodontal examination: Number of teeth present, probing pocket depth, clinical attachment level, bleeding on probing, and Plaque Control Record.

(6) Questionnaire survey on QOL.

Table. Study Schedule

| Item | | Study initiation | Period of periodontal treatment | Observation period | |
| --- | --- | --- | --- | --- | --- |
| Timing | | Week 0 | Less than 2 months | After 3 months | After 6 months |
| Examination | | Examination 1 | Examination 2–5 | Examination 6 | Examination 7 |
| Consent obtained | |  |  |  |  |
| Confirmation of patient characteristicsa | |  |  |  |  |
| Oral hygiene instruction | |  |  |  |  |
| Periodontal treatment | |  |  |  |  |
| Confirmation of subjective and objective symptoms | |  |  |  |  |
| Questionnaire survey on QOL | |  |  |  |  |
| Clinical tests | Blood testsb |  |  |  |  |
| Blood biochemistry  testsc |  |  |  |  |
| Periodontal examination | |  |  |  |  |

Open circles () indicate measures that will be performed prior to dental intervention. Black circles () indicate measures that will be performed after dental intervention.

aPatient characteristics indicate characteristics routinely noted in medical care, such as age, sex, past medical history, and complications.

bBlood tests indicate the same tests performed during regular medical examination.

cBlood biochemistry tests indicate the same tests performed during regular medical examination. In addition, factors associated with oxidative stress will be assessed to confirm the relationship between oral health and whole body status.

9. Discontinuation criteria

- 1. A subject asks to stop participating in the study or withdraws consent.
  2. It is found after enrollment that eligibility requirements are not fulfilled.

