  3. Continuation in the study is difficult due to exacerbation of complications.
  4. A subject is discovered to be pregnant.
  5. The entire study is discontinued.
  6. Dental treatment is found to be necessary for a subject in the oral hygiene instruction group after assignment.
  7. A physician determines that discontinuation is advisable for some other reason.

10. Handling when an adverse event occurs

(1) Response to patients when an adverse event occurs

When an adverse event that requires treatment occurs in a subject, the subject will be notified and appropriate medical care for the adverse event will be provided.

(2) Report of a serious adverse event

If a serious adverse event occurs or there is concern of such an event occurring, a report will be made immediately to the Hospital Director of Okayama University Hospital.

11. Report of deviation from protocol

The following matters are provided in accordance with GCP:

- The principal investigator and co-investigators will not deviate from or make changes to the study protocol before obtaining approval from the Hospital Director based on advance review of the Ethics Committee.
- The principal investigator and co-investigators may deviate from or change the study protocol before obtaining advance approval from the Ethics Committee for compelling reasons in order to avoid an emergency. In such cases, the principal investigator or a co-investigator will submit the details regarding the deviation or change and the associated reasons, together with a proposal for revision of the study protocol if necessary, to the Ethics Committee without delay, and approval from the Ethics Committee and Hospital Director will be obtained.
- In cases of deviation from the study protocol, the principal investigator or a co-investigator will record all items of deviation and the reasons for them.

12. Completion, discontinuation, or cessation of study

(1) Study completion

At the completion of the study, the principal investigator will submit a study completion report to the Hospital Director without delay.

(2) Study discontinuation or cessation

The principal investigator will consider whether or not to continue the study in the event of either of the following:

1) Recruiting subjects is difficult and reaching the planned number of subjects is judged to be unlikely.

2) The Ethics Committee asks for changes to be made in the protocol or other matters, and those changes are judged to be difficult to make.

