When a decision is made to discontinue or cease the study, a report to that effect together with the reason will be made in writing to the Hospital Director without delay.

13. Study period

From March 1, 2014 to March 31, 2016.

14. Data aggregation and statistical analysis

Data analysis will be conducted from the following observations:

1) Role of plaque control instruction in type 2 diabetes patients: The significance of plaque control instruction will be investigated from a comparison between the start of the study and the time of reassessment in the oral hygiene instruction group, including its effect on QOL.

2) Significance of periodontal treatment: The effects of periodontal treatment in type 2 diabetes patients will be discerned from a comparison of the oral hygiene instruction group and the non-surgical periodontal treatment group.

15. Target patient number and rationale

The target patient number is 20 for each group (40 patients total).

The number of patients is calculated to be 20 based on analysis of the serum HbA1c level in a previous study (see reference) on periodontal treatment in diabetes patients. To determine the sample size when the *t*-test is used, calculations were performed using SPSS Samplepower (IBM, Tokyo, Japan). Under the conditions of α=0.05 and β=0.20, with a two-tailed *t*-test, the predicted HbA1c level was 7.31% in the oral hygiene instruction group and 6.51% in the non-surgical periodontal treatment group. With an assumed standard deviation of 0.8, significance was hypothesized when the mean serum HbA1c differed by 0.8% as a result of periodontal treatment. As a result, 17 patients are needed for the study. Assuming a 15% dropout rate, the number is set at 20 patients.

16. Subjects’ rights, safety, and disadvantage

(1) Human rights (protection of privacy)

Subject data are coded and test results are provided to the person conducting the analysis at Okayama University so that individual subjects cannot be identified. To combine the data from the examination table, questionnaire, and each test, the same symbols are given to the same subject being examined. After the study has been completed, these data will be destroyed.

(2) Patient safety, disadvantage

Health insurance and other measures needed to compensate for health damage to subjects are not adopted.

Reason: There is the possibility only of slight pain when blood is taken. No damage to health is foreseen.

17. Cost to patients

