Within the range of regular medical examination.

18. Expected benefit from participating in clinical study, and possible risks

A benefit from participating in this study is that subjects are given a 2,000 yen QUO card as remuneration each time they undergo medical examinations. A disadvantage is that each test takes time. There is no risk.

19. Compensation for damage to health

Health insurance and other measures needed to compensate for health damage to subjects are not adopted.

Reason: This study is performed within the range of regular medical examination, and no damage to the subjects’ health is foreseen.

20. Correspondence with GCP and Helsinki Declaration

This study will be conducted in accordance with GCP and adhere to the principles laid down in the Helsinki Declaration (2008 revision).

21. Storage of records

The principle investigator will keep all required documents related to conducting this study (copies of application forms, correspondence from Hospital Director, copies of all applications and reports, subject identification code list, consent forms, copies of case reports, and other documents or records needed to guarantee the reliability of data) and dispose of them after the study has been published.

22. Publication of study results

The study results will be compiled in a report by April 30, 2016, and reported to the Hospital Director. The study results will also be used in journal publication(s) and conference presentation(s). When the study results are made public, personal information that could be used to identify individual subjects will not be disclosed.

23. Research organization

Affiliation: Department of Preventive Dentistry, Okayama University Graduate School of Medicine, Dentistry and Pharmaceutical Sciences

Title: Professor

Name: [name]

Affiliation: Department of Public Health, Okayama University Graduate School of Medicine, Dentistry and Pharmaceutical Sciences

Title: Professor

Name: [name]

Affiliation: Department of Nephrology, Rheumatology, Endocrinology, and Metabolism, Okayama University Graduate School of Medicine, Dentistry, and Pharmaceutical Sciences

Title: Associate Professor

Name: [name]

Affiliation: Preventive Dentistry, Okayama University Hospital

Title: Lecturer

Name: [name]

Affiliation: Preventive Dentistry, Okayama University Hospital

Title: Lecturer

Name: [name]

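### Safety is set aside and the protocol states no risk, yet its risk text never addresses the periodontal procedure given to one arm, and no adverse-event outcome by arm is planned

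*Protocol*

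**What the plan says.** Under section 7 (Assessments), the item "3) Safety assessment" is entered as not applicable. Section 18, on benefits and risks, closes with "A disadvantage is that each test takes time. There is no risk". Section 16(2), explaining why no compensation cover is arranged, says "There is the possibility only of slight pain when blood is taken. No damage to health is foreseen". Section 19 gives a similar reason: the study stays within routine medical examination.

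The two arms differ by a procedure. In the section 6(2) flow chart the treatment arm "Receives oral hygiene instruction + scaling and root planning, professional toothbrushing and mechanical tooth cleaning", while the other arm gets instruction alone.

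The protocol does provide for events. Section 10(1): "When an adverse event that requires treatment occurs in a subject, the subject will be notified" and given care. Section 10(2): "If a serious adverse event occurs or there is concern of such an event occurring, a report will be made immediately to the Hospital Director". Section 9 lists worsening complications among the reasons for discontinuation. Section 8(2) includes a symptom check: "Confirmation of subjective and objective symptoms: Confirmation by interview (with reference to the symptom diary if available". Section 14 names two analyses, a before-after look within the instruction arm and a comparison of the arms for the effects of periodontal treatment. It names no harm outcome.

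**The concern.** A protocol often leaves the layout of safety tables to an analysis plan. Here it goes further and rules safety assessment out, so an analysis plan that followed section 7(3) would have nothing to tabulate.

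The risk statements also look in the wrong place. The only discomfort named is that of blood sampling, which section 6(2) describes as routine and which both arms undergo. The procedure that is randomised appears in none of them.

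Two things are at stake. Section 2 wants the results to support bringing periodontal treatment into insured care, and as planned they would describe benefit without a matching account of harm. In addition, section 10(1) is triggered only by events that need treatment, and section 10(2) only by serious ones. An event that is neither has no stated route into the trial's results.

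**Working it through.** **1. The statements side by side**

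| Section | What it does about harm | Covers the periodontal procedure? |
|---|---|---|
| 7(3) | Safety assessment not applicable | No |
| 16(2) | Slight pain at blood sampling only | No |
| 18 | Time taken by tests; no risk | No |
| 19 | No health damage foreseen; routine examination | No |
| 10(1) | Care for events that need treatment | Not named; no recording rule |
| 10(2) | Immediate report of serious events | Not named |
| 8(2) | Symptom interview | Not named; tied to no outcome |

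Sections 16(2) and 18 conflict directly: one foresees slight pain, the other no risk. On harm from scaling and root planing the protocol is silent rather than contradictory.

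**2. Does routine care cover the procedure?** Section 4(2) excludes patients already undergoing dental treatment, and section 6(10) assigns the arms from a table of random numbers. For these patients the trial itself introduces the procedure, so the reason given in section 19 does not reach it.

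**3. What harm-related data would exist?**
- Symptoms by interview (8(2)).
- Withdrawals, discontinuations and dropouts (6(10)).
- Changes in diabetes treatment (6(2)).
- Serious-event reports (10(2)).
- Endpoints that can move in the wrong direction, such as HbA1c, attachment level, bleeding on probing, tooth count and QOL (7).

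None of these is an adverse-event outcome. Discontinuations are a poor substitute, because section 9 item 6 (need for dental treatment) applies to the instruction arm only, so the counts are not like for like.

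**4. The denominator.** Section 15 gives a difference of 7.31 − 6.51 = 0.80, SD 0.8, two-sided α = 0.05 and power 0.80. The standardised difference is 0.8/0.8 = 1.0. A two-sample t-test then needs 16.71 per group, rounded up to 17 (power 0.807), and 17/0.85 = 20. The protocol's figures reproduce.

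**5. What clean data could show.** With 0 events in n patients, the one-sided 95% upper limit is 1 − 0.05^(1/n).
- n = 20: 1 − 0.05^(1/20) = 0.139.
- n = 17 (after the assumed 15% dropout): 1 − 0.05^(1/17) = 0.162.

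**6. What a formal test could show.** Power of Fisher's exact test, two-sided 0.05, 20 per arm, summed over all outcome pairs with p ≤ 0.05. The event rates are assumptions; the documents give none.

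| Treatment arm | Instruction arm 0% | Instruction arm 5% |
|---|---|---|
| 20% | 0.37 | 0.17 |
| 30% | 0.76 | 0.45 |
| 40% | 0.95 | 0.72 |

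Only large differences would be detected, so a test adds little to a table.

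**The case against.** The strongest reply is that the gap is narrower than it first looks. Much of this stands.

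A reader might infer that the trial would hold no harm data at all, or that harm could not be compared. The documents do not support that: the items in step 3 of the working are collected and not limited to one arm. What is missing is a specified outcome and a tabulation.

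A reader might also infer that patients are told there is no risk. Section 18 is protocol text. Section 5 refers to a separate consent form approved by the ethics committee, which is not available here, so nothing can be said about its content.

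Nor is section 10 strong evidence of contradiction. Saying what to do if an event occurs is compatible with not expecting one, and the worsening complications in section 9 are not attributed to the intervention.

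The 14% limit reflects the size of the trial and would hold with or without a safety outcome. A table from 40 patients would not settle the harm side of an insurance decision.

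Finally, the circles in the schedule table could not be read in the copy used, so it is unknown whether the symptom check falls within the treatment period (examinations 2–5).

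None of this removes two facts: safety assessment is ruled out by a positive entry, and the only procedure that differs between the arms appears in no risk statement.

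**Conclusion.** The point holds as a gap in the planned outcomes together with risk text that needs reconciling. It should be corrected, but it does not threaten the trial's main result: no efficacy endpoint, sample size or error rate changes.

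All patients in the treatment arm, 20 as planned, are to receive the procedure within about two months, and none of its non-serious harms is a named outcome. The flat statement of no risk could not be supported even by a clean record, since 0 of 20 is compatible with a true rate of up to about 14% (about 16% with 17 completers). Those limits are exact binomial and rest only on the planned numbers. The power figures rest on assumed event rates and serve only to show why a formal test is not worth planning.

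**What to change.** 1. In section 7(3), replace the not-applicable entry with a descriptive safety outcome: all adverse events in both arms, whether or not they need treatment.
2. Record them at the section 8(2) symptom check, asked in the same way in both arms. Confirm that the check covers the treatment period, and extend the recording to those visits if it does not.
3. Tabulate events by arm, with numbers of patients and events, and make no formal comparison.
4. Reconcile sections 16(2), 18 and 19 with section 10, so that the protocol's risk text addresses the periodontal procedure and no longer says that there is none.

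The cost is one case report form page, one table and a protocol amendment, which section 26 requires the ethics committee to approve in advance. If the symptom check already covers the treatment visits, no visit is added. The sample size stays as it is.

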Sera will be separated from blood samples obtained during the course of this study and stored in a freezer at −80°C in a locked room in the medical office for use in the event that retesting is necessary. Anonymized treatment information will be kept on the principal researcher’s computer and statistically analyzed at the completion of the study.

(2) Storage duration

Treatment information will be kept for 5 years after the data are analyzed and the study is completed. Specimens measured after the completion of the study will be disposed of after the measurements, maintaining anonymity.

26. Changes to protocol

Changes (revisions) to the protocol or informed consent forms require advance approval of the Ethics Committee, Okayama University Graduate School of Medicine, Dentistry and Pharmaceutical Sciences and Okayama University Hospital.

27. Reference materials/reference list

